#### Data management and monitoring

A paper-based case report form will be composed before the study commences. Each variable is carefully coded for auditing and statistical analysis. The participants’ general information will be recorded in the case report form by the responsible investigator, whereas participant-reported information will be documented in the case report form by participants.

We will adopt a double data entry and double check approach to data management. All steps involved in the approach to data management will be independently conducted by two data administrators from the Pharmacoepidemiology and Statistics Research Center. If any inconsistency is identified in the data entry or logic consistence check, the investigators will be contacted for further information and clarification. To protect privacy, participants’ identification information (name, telephone, home address, and participants’ family member information) will not be used with the data management software.

The DSMB will review the analyses in terms of efficacy and safety. While the trial is ongoing, DSMB members have access to original data but are blinded to participant allocation. The principle role of the DSMB is to provide a written recommendation in a timely manner to the investigator to discontinue a trial following discussion and assessment of efficacy and safety data.

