### Statistical analysis plan

#### Sample size and power calculations

Sample size calculation was based on information from the Thai Renal Outcomes Research-Peritoneal Dialysis database collected between 2006 and 2016, with an estimated rate of 0.31 episodes per patient-year and 0.39 episodes per patient-year for exit-site infection and peritonitis, respectively (composite rate of PD-related infections of 0.70 episodes per patient-year) [3]. To detect an expected clinically relevant difference in both exit-site infection and peritonitis rate of 30% (0.70 episodes per patient-year vs. 0.49 episodes per patient-year) between our usual exit-site care with normal saline and interventions (either chlorhexidine gluconate-impregnated patch or mupirocin ointment), approximately 118 participants per group will be enrolled to obtain 80% power with a two-sided significance level of 0.05, while allowing for 25% all-cause dropout during the study period. Thus, the overall targeted minimum sample size will be 354 participants.

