#### Statistical analysis

Baseline characteristics will be summarized as number (percentage) or mean ± standard deviation, or medians with interquartile range as suitable. Differences between treatment groups will be compared using Fisher’s exact test and analysis of covariance (ANCOVA) or Kruskal-Wallis test for categorical and continuous variables, respectively. All analyses will be conducted on both a per-protocol and intention-to-treat basis. All analyses will be performed using Stata software version 14.0 (StataCorp, LP) and Microsoft Excel version 2016. They will be two-tailed, and a *P*-value less than 0.05 will be considered statistically significant.

For a primary analysis, Cox proportional hazards regression and Poisson regression analyses will be performed to assess the effectiveness of the chlorhexidine gluconate-impregnated patch and mupirocin ointment compared to usual exit-site care with normal saline for the first episode of PD-related infection and longitudinal rates, respectively. Secondary analysis using statistical methods as described above will then be analyzed to evaluate the effect on the prevention of PD-related infections between chlorhexidine gluconate-impregnated patch and mupirocin ointment. The treatment effects will be estimated as hazard ratios or incidence rate ratios with corresponding 95% confidence interval. Kaplan-Meier survival curves will be constructed for visual presentation of time-to-event comparisons.

Several a priori subgroup analyses with respect to the minimization variables for both primary and secondary outcomes will be investigated. For instance, the lists of variables include age (<65 vs. ≥65 years), gender, history of diabetes, history of PD-related infections (peritonitis or exit-site/tunnel infection), *S. aureus* colonization status (nasal or exit-site PD catheter), PD modality (continuous ambulatory peritoneal dialysis vs. automated peritoneal dialysis), PD vintage, and serum albumin (< 3.5 vs ≥3.5 mg/dL).

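### The DSMB must advise on stopping from efficacy and safety data while blinded to allocation, with no stated route to the treatment key

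*Protocol article*

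**What the plan says.** In the Protocol article, Data management and monitoring, the DSMB reviews both efficacy and safety. On access during the trial the section states that "DSMB members have access to original data but are blinded to participant allocation". The board's principal role is to give the investigator written advice "to discontinue a trial following discussion and assessment of efficacy and safety data". The section does not say whether the board's data are pooled or split by coded arm. It gives the board no route to the key, and it does not say whether efficacy findings may stop the trial for benefit.

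Two other sections bear on who learns allocation:

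- Safety monitoring and trial-related injury: after a serious adverse event, the investigator informs the DSMB and at once obtains that participant's allocation from the statistician.
- Blinding: unblinding is allowed in such cases, but investigators are to learn allocation only when the study ends.

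On the error rate, Statistical analysis says: "They will be two-tailed, and a *P*-value less than 0.05 will be considered statistically significant". Sample size and power calculations says that "approximately 118 participants per group will be enrolled to obtain 80% power with a two-sided significance level of 0.05", for "0.70 episodes per patient-year vs. 0.49 episodes per patient-year".

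**The concern.** A recommendation to stop for efficacy or safety rests on a comparison between known treatments. The section assigns that task and withholds the information it needs, without an exception. Over a long trial, an arm-specific harm could go unattributed, or a benefit over saline could be mistaken for harm.

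The separate rule for serious adverse events lets the investigator learn individual allocations while the oversight board stays blinded. This matters because the Blinding section lists outcome assessment among the physicians' tasks, although it also assigns assessment to a third party.

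The use of efficacy data also raises the question of whether interim looks could consume part of the 5% that the final tests use in full.

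**Working it through.** **1. The plan's own sample size.** Inputs, from Sample size and power calculations: 0.70 and 0.49, two-sided 0.05, 80% power, 25% dropout. Treating the two rates as proportions, with mean 0.595:

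- n = [1.96 × √(2 × 0.595 × 0.405) + 0.8416 × √(0.70 × 0.30 + 0.49 × 0.51)]² / 0.21² = 84.6, rounded up to 85.
- With continuity correction: (84.6 / 4) × [1 + √(1 + 4 / (84.6 × 0.21))]² = 93.9, rounded up to 94.
- With dropout applied as a multiplier: 94 × 1.25 = 117.5, rounded up to 118.

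Of the variants tried, only this one gives 118. It uses the full 0.05, so nothing is set aside for interim looks. Whether the method suits event rates is a separate matter.

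**2. What pooled data can show.** With saline at 0.70, both active arms at 0.49 and 1:1:1 allocation, the pooled rate is (0.70 + 0.49 + 0.49) / 3 = 0.56 per patient-year. Three identical arms at 0.56 give the same figure. The same reasoning applies to skin reactions or deaths: a pooled total does not place an excess in an arm.

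**3. What coded arms without a key can show.** Suppose the board reads A = 0.70, B = 0.49, C = 0.49.

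| If saline is | The same table means |
|---|---|
| A | Both active arms cut the rate by 30%, the effect the trial was designed to find |
| B or C | One active arm raises the rate by 0.70 / 0.49 = 1.43 times against saline, and the other has no effect |

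The imbalance is visible, but the two readings call for opposite conclusions.

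**4. How long this applies.** Enrolment began in September 2016 (Blinding) and was expected to finish in October 2019 (Trial status). Adding 24 months of follow-up gives October 2021, about five years.

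**5. Unblinding after a serious adverse event.** Safety monitoring and trial-related injury describes disclosure to the investigator as the procedure for such an event. Blinding only permits unblinding then, and also says investigators stay blinded until the end. The two sections cannot all be followed as worded.

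**6. Type I error, under assumption.** The document gives no number of looks, so 2 to 5 equally spaced analyses (including the final one) are assumed for one comparison. Simulation under the null, 1,000,000 runs:

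| Analyses | Every analysis at 0.05 | Interim at absolute z above 3, final at 0.05 |
|---|---|---|
| 2 | 8.3% | 5.1% |
| 3 | 10.7% | 5.1% |
| 4 | 12.6% | 5.2% |
| 5 | 14.2% | 5.3% |

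An absolute z above 3 is a two-sided P of about 0.0027. A threshold of P<0.001 is stricter, so its error lies between 5.0% and the last column. If no look compares arms, or none can stop for benefit, the error stays at 5%.

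**The case against.** The strongest reply is that blinding to participant allocation is compatible with reports by coded arm. A reader might infer that the board cannot compare arms at all; the text does not support that, because it never says the data are pooled. This part of the objection stands. It does not dispose of the point, since step 3 shows that a code without a key still leaves the direction of an effect unknown. For skin reactions a board might guess which code is an active arm. For infections and deaths a guess is not a sound basis for advice.

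A reader might also infer that the final 5% is unprotected. That is not supported either. The article fixes no interim test, number of looks or rule for stopping for benefit, and efficacy data can also inform futility or harm. Looks and boundaries are commonly left to an analysis plan or board charter, neither of which is shown, so their absence is no error. Keeping 0.05 at the end is compatible with a strict interim boundary.

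The two consequences are also alternatives. A board that sees only pooled data cannot inflate the error of an arm comparison. A board that sees arms raises the error question only if it can stop for benefit.

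Finally, disclosure after a serious adverse event concerns one participant at a time and says nothing about what the board receives. That is fair, and the conflict between those sections is secondary. It is still a conflict in the text.

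**Conclusion.** The point holds in this form: the article states a rule, rather than leaving a gap, under which the board is to advise on discontinuation from efficacy and safety data while blinded to allocation for as long as the trial runs. Pooled data cannot locate a harm in one of three arms, and coded data without a key cannot separate harm from benefit. Neither result depends on an assumed number of looks. The illustration in steps 2 and 3 uses the plan's own rates. A charter that gives the board the key on request would meet the need, but the published wording provides for none.

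The type I error point is conditional. Inflation is zero if no look can stop for benefit and small under a strict boundary. Only with 2 to 5 analyses each tested at an unadjusted 0.05 does the error for one comparison reach 8.3% to 14.2%.

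**What to change.** - Amend Data management and monitoring so that an independent statistician supplies the DSMB with closed reports by coded arm (A/B/C), with the key available to the board on request, while investigators and outcome assessors stay blinded.
- Reconcile Safety monitoring and trial-related injury with Blinding on who learns allocation after a serious adverse event, and when.
- State whether efficacy review may stop the trial for benefit. If it may, set a strict interim threshold, for example Haybittle-Peto at P<0.001, so that the 0.05 in the sample size and the final analysis can stand. If it may not, say so; no adjustment is then needed.

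The cost is a change of wording in the protocol and the board's charter, plus extra closed-report tables. No participants are added. The downside is that, with a strict threshold, early stopping for benefit becomes harder.

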#### Statistical analysis

Baseline characteristics will be summarized as number (percentage) or mean ± standard deviation, or medians with interquartile range as suitable. Differences between treatment groups will be compared using Fisher’s exact test and analysis of covariance (ANCOVA) or Kruskal-Wallis test for categorical and continuous variables, respectively. All analyses will be conducted on both a per-protocol and intention-to-treat basis. All analyses will be performed using Stata software version 14.0 (StataCorp, LP) and Microsoft Excel version 2016. They will be two-tailed, and a *P*-value less than 0.05 will be considered statistically significant.

For a primary analysis, Cox proportional hazards regression and Poisson regression analyses will be performed to assess the effectiveness of the chlorhexidine gluconate-impregnated patch and mupirocin ointment compared to usual exit-site care with normal saline for the first episode of PD-related infection and longitudinal rates, respectively. Secondary analysis using statistical methods as described above will then be analyzed to evaluate the effect on the prevention of PD-related infections between chlorhexidine gluconate-impregnated patch and mupirocin ointment. The treatment effects will be estimated as hazard ratios or incidence rate ratios with corresponding 95% confidence interval. Kaplan-Meier survival curves will be constructed for visual presentation of time-to-event comparisons.

Several a priori subgroup analyses with respect to the minimization variables for both primary and secondary outcomes will be investigated. For instance, the lists of variables include age (<65 vs. ≥65 years), gender, history of diabetes, history of PD-related infections (peritonitis or exit-site/tunnel infection), *S. aureus* colonization status (nasal or exit-site PD catheter), PD modality (continuous ambulatory peritoneal dialysis vs. automated peritoneal dialysis), PD vintage, and serum albumin (< 3.5 vs ≥3.5 mg/dL).

To address robustness of the treatment effects, further sensitivity analyses of the primary analysis will be performed by (i) adjusting for the several baseline covariates that seem to affect the outcomes (age, history of diabetes, history of PD-related infections, *S. aureus* colonization status, PD modality, PD vintage, and serum albumin); (ii) restricting the analysis to only PD-related infection episodes with positive cultures to account for misclassification bias; (iii) using the proportional sub-distribution hazards analyses by Fine and Gray method to address the completing risk outcomes, including mode switching to long-term hemodialysis, kidney transplantation, conservative treatment, or death; and (iv) using the multiple imputation method to evaluate the effect estimates when missing data are indicated.

Moreover, we will conduct a cost-utility analysis alongside the trial. Resource use will be collected using a standard Excel-based costing tool. Healthcare costs will be estimated from patient and societal perspectives and will be expressed in Thai Baht and USD. We will consider direct medical costs, direct nonmedical costs, and indirect costs. Utility values will be estimated for each patient using the EQ-5D-5 L instrument [30]. The EQ-5D-5 L is a five-dimension quality of life instrument designed to elicit utility values for a patients’ current health status. It will be completed at five time points. Responses to the EQ-5D-5 L will be scored using preference weight estimates from Thai populations, [33] which convert the five responses into a single summary index, where a score of one reflects perfect health, and zero is equivalent to dead. We will use a Markov simulation model to estimate the total costs and health outcomes in terms of clinical events and quality-adjusted life years (QALYs) over the patient lifetime (i.e., 20 years). Cost and health outcomes beyond the trial will be derived from a systematic review and from health administrative reports containing information about progression of the disease in Thailand (Fig. 2). As per Thai Health Technology Assessment guidelines, costs and health outcomes will be discounted at an annual rate of 3% [34]. The results of the economic evaluation will be presented as incremental cost-effectiveness ratios comparing the total costs and QALYs among treatment groups. Thai Baht and UDS per QALYs gained will be illustrated. A series of deterministic and probabilistic sensitivity analyses will be performed to evaluate the robustness of the cost-effectiveness estimates and study assumptions. Probabilistic sensitivity analyses results will also be used to create cost-effectiveness acceptability curves, which represent the probability of a treatment being cost-effective to a range of potential threshold values that the decision makers may be willing to pay for an additional unit of effect.

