To date, few RCTs have identified the optimal antimicrobial agent or alternative strategies for the prevention of PD-related infection. Although antimicrobial resistance with routine use is a concern, no RCTs have compared topical antimicrobial agents with usual exit-site care for the prevention of PD-related infections among the Thai PD population. In the COSMO-PD (Chlorhexidine glucOnate verSus Mupirocin Ointment in the prevention of Peritoneal Dialysis-related infection) trial, we aim to assess the safety, efficacy, and cost-effectiveness of a chlorhexidine gluconate-impregnated patch, mupirocin ointment, and usual exit-site care with normal saline dressing in preventing PD-related infections. We hypothesize that the chlorhexidine gluconate-impregnated patch or mupirocin ointment will be superior to usual exit-site care with normal saline in terms of the efficacy and cost utility of the interventions.

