### Outcomes

#### Primary outcome

The primary outcomes of the COSMO-PD trial are time-to-first PD-related infection (exit-site/tunnel infection or peritonitis) event and overall difference in PD-related infection rates between study arms. PD-related peritonitis and exit-site/tunnel infection will be defined according to the ISPD guidelines [2, 7]. Participants will be diagnosed as having peritonitis if they meet at least two of the following criteria: (i) clinical features (e.g., abdominal pain and/or cloudy dialysis effluent); (ii) dialysate effluent white cell count more than 100 cell/μL (after a dwell time of at least 2 h), with polymorphonuclears making up more than 50%; and (iii) positive dialysis effluent culture. Exit-site infection and tunnel infection will be indicated as the presence of purulent discharge (with or without erythema of the skin) and evidence of collection along the catheter tunnel (clinical inflammation or ultrasonographic), respectively.

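### Two primary outcomes on two active-versus-saline contrasts are each tested at 0.05 with no rule for which result decides, so about 14–15% of null trials give at least one significant primary test

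*Protocol article*

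**What the plan says.** All references are to the protocol article.

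- **Primary outcome.** Two are named: "time-to-first PD-related infection (exit-site/tunnel infection or peritonitis) event" and "overall difference in PD-related infection rates between study arms". They are joined by *and*, with no statement on whether one or both must succeed.
- **Statistical analysis.** "For a primary analysis, Cox proportional hazards regression and Poisson regression analyses will be performed", the first for the first episode and the second for longitudinal rates, each comparing chlorhexidine and mupirocin with saline. Chlorhexidine versus mupirocin is secondary and lies outside this point. All analyses are run on both the per-protocol and the intention-to-treat set. On the tests: "They will be two-tailed", and a P-value "less than 0.05 will be considered statistically significant".
- **Background.** "We hypothesize that the chlorhexidine gluconate-impregnated patch or mupirocin ointment will be superior to usual exit-site care with normal saline". The *or* here links the two products, not the two outcomes.
- **Sample size and power calculations.** One pairwise comparison of infection rates (0.70 versus 0.49 per patient-year) is sized for "80% power with a two-sided significance level of 0.05".
- **Study withdrawal.** This section describes how data from withdrawn participants enter the intention-to-treat analysis, but does not say that this analysis decides.

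No section gives an alpha split, a testing order, a global test or a rule requiring both outcomes.

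**The concern.** Two outcomes on two contrasts make four primary tests per analysis set, each with the full 5%. A hypothesis that one product or the other is superior is supported by a single win. The stated 0.05 is therefore the error rate of each test, not of the trial's main claim.

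The second problem is practical. At the planned effect the two models have quite different power, so they will often disagree. When Cox and Poisson differ, or intention-to-treat and per-protocol differ, the article does not say which is the trial's result. A conclusion about routine exit-site care in Thai PD patients could then rest on a choice made after the data are seen.

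**Working it through.** **1. The plan's own sample size.** Inputs from the sample size section: 0.70 versus 0.49, two-sided 0.05, 80% power, 25% dropout. Treating the two rates as proportions, with mean 0.595 and difference 0.21:

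n₀ = [1.96·√(2·0.595·0.405) + 0.842·√(0.70·0.30 + 0.49·0.51)]² / 0.21² ≈ 84.6

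Continuity correction: (n₀/4)·[1 + √(1 + 4/(n₀·0.21))]² ≈ 93.9, so 94. Then 94 × 1.25 = 117.5, rounded up to 118, the stated figure. It is a single comparison at the full 0.05. With the same formula at 0.025, n is 112, and 112 × 1.25 = 140 per group. The stated size thus leaves no allowance for more than one primary test. (Whether rates should be handled as proportions is a separate matter.)

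**2. Simple bounds for four tests at 0.05.** If independent, 1 − 0.95⁴ = 18.5%. Whatever the dependence, at most 4 × 0.05 = 20%.

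**3. Allowing for the shared control.** With 1:1:1 allocation, the two contrasts correlate at 0.5 under the null. The correlation ρ between the Cox and Poisson statistics within a contrast is not in the article, so the four-variate normal result is given over a range:

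| ρ | At least one of four significant, either direction | At least one false superiority |
|---|---|---|
| 0 | 17.3% | 8.9% |
| 0.5 | 16.1% | 8.1% |
| 0.7 | 14.8% | 7.4% |
| 0.8 | 13.9% | 7.0% |
| 0.9 | 12.6% | 6.3% |
| 0.999 | 9.4% | 4.7% |

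**4. Simulation at the protocol's figures.** 118 per arm, 0.70 episodes per year in all arms, 24 months, 25% dropout at a constant hazard (the dropout pattern is an assumption), no between-patient variation, log-rank as the Cox score test, and a Poisson rate test.

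- ρ is about 0.74.
- At least one of the four tests significant: 14.2% to 14.8% across separate simulations.
- At least one false superiority: about 7%, against a nominal 2.5%.
- One contrast, either outcome: about 8%.
- Both outcomes required within a product, either product: about 3.5%.

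**5. Disagreement between the models.** In the same set-up at the planned effect (0.70 versus 0.49), a single contrast has about 57% power by Cox and about 78% by Poisson. The two reach different verdicts in about 26% of trials.

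**6. Power cost of Holm's first step.** Patient-years per arm are about 205 (118 with the constant-hazard dropout above). z = ln(0.70/0.49) / √[(1/0.70 + 1/0.49)/205] = 0.357/0.130 ≈ 2.74. Power at 0.05 is Φ(2.74 − 1.96) ≈ 78%. Power at 0.025 is Φ(2.74 − 2.24) ≈ 69%.

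**The case against.** **Multiplicity rules are often left to an analysis plan that is not shown here.** True in general. But this article is not silent: it fixes 0.05 for all analyses and sizes one comparison at the full 0.05. An adjustment elsewhere would change what is stated here.

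**The 14–15% is not the chance of a false win.** This stands. The figure counts significance in either direction, as two-tailed testing does. The hypothesis concerns superiority, and for that event the figure is about 7% against 2.5%.

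**The outcomes are joined by *and*, so perhaps both must succeed.** Under that rule the error would be about 3.5%. A reader might equally infer that any one win suffices, taking the Background's *or* to cover the outcomes. The article states neither rule, and the gap between about 3.5% and about 14–15% is why one is needed.

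**Two different products against a shared control may need no joint adjustment.** This is a fair position, and adjustment across products is a matter of judgement. It does not remove the point: two primary outcomes alone take each product to about 8%. The Background also states one joint hypothesis.

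**The error might be put at 15% or more, even 20–26%.** A reader might infer this by allowing infections to cluster within patients. The article gives no between-patient variance. The 20–26% arises at assumed variances of 0.25–0.5 with plain Poisson standard errors, which make the Poisson test itself too liberal. With robust errors the figure returns to about 15–16%. That is a variance problem, not multiplicity. Nor is 15% a floor, since the range with valid tests runs from about 9%.

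**Both outcomes are prespecified and the article commits to multi-arm CONSORT reporting.** This makes concealing one result less likely, but does not say which result decides when they differ.

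**Conclusion.** The point holds. Followed as written, the plan does not keep its primary claim at 5%. Under the null, with no overdispersion, at least one of four primary tests is significant in about 14–15% of trials, within 9–17% over the unknown outcome correlation. False superiority of at least one product is about 7% against 2.5%. If each product is taken as its own question, the error is about 8% per product. These figures rest on the protocol's rate, follow-up and dropout, on the shared saline arm, and on reading any one significant primary test as support for the hypothesis. They cover one analysis set; the per-protocol repeat is not quantified.

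The documents do not support a minimum of 15%, or 20–26% as the effect of multiplicity. With about 26% of trials expected to show discordant Cox and Poisson verdicts at the planned effect, the missing decision rule is likely to matter in practice.

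**What to change.** Before unblinding:

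1. Name the infection rate, the quantity used for sizing, as the sole primary outcome. Analyse it with robust or negative binomial variance so that its 0.05 holds. This is needed because a rate-only Holm procedure with plain Poisson errors still gave a familywise error of about 10–14% at assumed between-patient variances of 0.25–0.5.
2. Make time to first infection key secondary, tested for a product at the same alpha only after that product wins on the rate.
3. State that intention-to-treat decides and per-protocol is supportive.
4. If the joint either-product hypothesis is kept, apply Holm to the two rate contrasts (0.025, then 0.05). Holm then protects the two rate claims. If the key secondary tests are to share the same 5%, release the full 0.05 to the second product only after the first has passed both of its tests.

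Cost: this changes a published primary outcome during enrolment (288 of 354 randomised by July 2019, according to Trial status), so it must be a dated amendment and not just analysis-plan wording. Investigators are to be unblinded only at the end of the study, so the change can still be made credibly. Holm's first step lowers single-contrast power on the rate from about 78% to about 69% with no overdispersion. The one-outcome and intention-to-treat rules cost no power on the rate. A both-outcomes-required rule or an alpha split would keep both outcomes primary, at a cost in power.

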### Randomization and allocation concealment

Eligible participants will be randomized with a 1:1:1 allocation ratio to receive the interventions. Randomization will be conducted by a blinded member of the research team using random permuted blocks stratified according to the history of PD-related infections (exit-site/tunnel infection or peritonitis) and the study setting. A list of numbers will be generated by copyrighted software (available at http://www.randomizer.org). The randomization blocks will be blinded to the investigators. Each study setting will be concealed using opaque envelopes opened only upon recruitment of an individual consented participant.

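### Poisson regression is named for the primary repeat-infection rate with no stated allowance for risk differing between patients; with default standard errors, any residual difference makes the intervals too narrow

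*Protocol article*

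**What the plan says.** The Primary outcome section names two primary outcomes: time to first PD-related infection, and the "overall difference in PD-related infection rates between study arms". The Statistical analysis section states that "Cox proportional hazards regression and Poisson regression analyses will be performed to assess the effectiveness" of the two active products against saline, "for the first episode of PD-related infection and longitudinal rates, respectively". Cox therefore takes first events, and Poisson takes the rate with all episodes. Results are to be reported as hazard ratios or incidence rate ratios with 95% confidence intervals, at a two-sided 0.05 level.

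No variance estimator, dispersion check or patient-level term is named for the Poisson model.

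Two other places bear on whether patients share one rate. Randomization is "stratified according to the history of PD-related infections (exit-site/tunnel infection or peritonitis) and the study setting". The first of the four sensitivity analyses adjusts for age, diabetes, infection history, *S. aureus* colonization, PD modality, PD vintage and albumin, on the ground that these appear to influence the outcomes. The other three are culture-positive episodes only, Fine and Gray, and multiple imputation.

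**The concern.** Model-based Poisson standard errors are valid when the variance of a patient's episode count equals its mean, that is, when patients in an arm differ only through follow-up time and modelled covariates. If some patients are more infection-prone than others, counts vary more than that and episodes cluster within patients. The model-based standard error is then too small.

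The article's own covariate list implies that such differences are expected, yet adjustment appears only as a sensitivity analysis. Adjustment also removes only the part of the variation that the listed covariates explain. None of the other three sensitivity analyses deals with within-patient correlation.

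At stake are the interval and P value for a primary outcome on which superiority of chlorhexidine or mupirocin over saline could be claimed.

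**Working it through.** **Inputs from the article** (Sample size and power calculations, unless noted)
- Usual-care rate: "composite rate of PD-related infections of 0.70 episodes per patient-year". Target contrast: "0.70 episodes per patient-year vs. 0.49 episodes per patient-year".
- 118 per arm, "to obtain 80% power with a two-sided significance level of 0.05", "while allowing for 25% all-cause dropout during the study period".
- Follow-up to 24 months (Abstract).

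**Assumptions, not in the article**
- Dropouts contribute half the period on average, so mean follow-up is 2 × (0.75 + 0.25 × 0.5) = 1.75 years.
- Each patient's rate is the arm rate times a multiplier with mean 1 and variance k, with k = 0, 0.25, 0.5 or 1.0.

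**1. The plan's own figure.** On the log-rate scale, patient-years per arm = (1.96 + 0.8416)² × (1/0.70 + 1/0.49) / (ln 0.70)² = 7.849 × 3.469 / 0.1272 ≈ 214. Dividing by 1.75 gives 122 per arm. The rate-difference and square-root versions need 212 and 210 patient-years, so 121 and 120 per arm. The planned 118 gives 118 × 1.75 = 206.5 patient-years and about 78.6% power, close to the stated 80%. The figure also arises exactly if the two rates are entered as proportions with a continuity correction: 94 × 1.25 = 117.5, rounded up to 118. The article does not say which route was used. Neither contains an allowance for extra-Poisson variation.

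**2. Repeat episodes are common.** A usual-care completer expects 0.70 × 2 = 1.4 episodes. Even under a pure Poisson process, the chance of two or more is 1 − e^(−1.4) × (1 + 1.4) ≈ 41%.

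**3. Size of the understatement.** With mean count μ = 0.70 × 1.75 = 1.225, the true variance is μ + kμ², so the variance factor is φ = 1 + 1.225k. The model-based standard error is 1/√φ of the true one, and the actual type I error is 2[1 − Φ(1.96/√φ)]. A simulation (118 per arm, exponential dropout reaching 25% at 24 months, gamma multipliers, no true effect, 20,000 runs) checks this for one active arm against saline.

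| k | φ | SE ratio | Type I, formula | Type I, simulated | Type I, robust SE |
|---|---|---|---|---|---|
| 0 | 1.00 | 1.00 | 5.0% | 5.1% | 5.3% |
| 0.25 | 1.31 | 0.87 | 8.6% | 8.8% | 5.2% |
| 0.5 | 1.61 | 0.79 | 12.3% | 12.6% | 5.2% |
| 1.0 | 2.23 | 0.67 | 18.9% | 19.9% | 5.8% |

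For scale, a binary factor that splits patients in half with a threefold rate difference (rates 1 and 3: mean 2, variance 1) gives k = 1/2² = 0.25. A twofold difference (rates 1 and 2: mean 1.5, variance 0.25) gives k = 0.25/1.5² = 0.11 and a type I error of about 6.6%.

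**4. Effect of stratified randomization.** Variation explained by a balanced stratum does not add to the true variance of the arm contrast. With a perfectly balanced 50/50 stratum assumed to explain none, half or three-quarters of k, simulated type I error of the model-based test is:

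| k | None | Half | Three-quarters |
|---|---|---|---|
| 0.25 | 9.2% | 7.4% | 6.4% |
| 0.5 | 13.1% | 9.4% | 7.2% |
| 1.0 | 19.8% | 13.7% | 9.6% |

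**5. Power once the variance is right.** The variance of the log rate ratio is 3.469/206.5 + 2k/118, and power is Φ(0.3567/SE − 1.96).
- k = 0: SE 0.130, power 79%.
- k = 0.25: SE 0.145, power 69% (simulated 68%).
- k = 0.5: SE 0.159, power 61% (simulated 60%).
- k = 1.0: SE 0.184, power 49% (simulated 48%).

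**The case against.** The strongest reply is that the article never says the standard errors are model-based. Poisson regression with patient-level robust errors is still Poisson regression and fits the text as written. The article is also condensed from a full protocol that is not at hand, and a variance option is the kind of detail an article may leave out. This stands as far as it goes: a reader might infer that a plain, uncorrected Poisson fit has been fixed, and the text does not support that inference. It does not remove the point. This section goes as far as the software version, Fine and Gray and multiple imputation, yet names a model for repeat events without the property that makes its inference valid. A default fit of the named model would give the narrow interval.

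Four further limits are fair:
- The inflation depends on a dispersion that the article does not give.
- Stratified randomization reduces it, so the figures in step 3 are upper values for each k.
- The article gives no reason for stratifying on infection history. The choice is consistent with differing risk but is not a stated belief about it.
- A reader might cite simultaneous exit-site infection and peritonitis as a source of dependence. The article does not say that they occur together or how they would be counted, so nothing here rests on that.

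**Conclusion.** The concern holds in conditional form. The article names Poisson regression for a primary rate that counts repeats and states no allowance for between-patient heterogeneity, while its own sections treat baseline factors as affecting risk. If model-based standard errors are used and residual heterogeneity exists, the rate-ratio intervals are too narrow. Per-comparison type I error is then about 9%, 12-13% or 20% at assumed variances of 0.25, 0.5 or 1.0. It is lower where the stratification factors explain part of the variance, and 5% if there is none.

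The stronger reading, that false-positive claims will exceed 5%, is not established: it needs both conditions, and the article settles neither. Nor does the problem reach both primary outcomes. The Cox analysis uses each patient's first infection only and is untouched.

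**What to change.** State in the analysis plan, before unblinding, that the primary rate model is negative binomial regression with log patient-years on PD as offset, or Poisson regression with the same offset and patient-level robust (sandwich) standard errors. Keep model-based Poisson at most as a sensitivity analysis. Because stratification balances part of the variation, an unadjusted robust analysis would err towards caution; including the stratification factors as covariates in the primary model would recover that.

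The change takes one sentence and one software option. Almost nothing is lost without overdispersion: robust power is about 79%. If overdispersion is present, intervals widen and power at 118 per arm falls to about 68% or 60% at variances of 0.25 or 0.5. Report power as that range, with the variances labelled as assumptions.
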